#### Steering committee

A steering committee will be comprised of a member of the research team, a student member of the research team, a clinical program director of pediatric services related to mobility, an occupational therapist who works with children who use MWCs, a child educator with bioethical training, a parent of a child who uses a wheelchair, a child (14 years +) who uses a MWC. There will be representation from all three cities involved in this trial. A statistician will be consulted by the primary investigator at mid-trial to perform an interim analysis. A decision to stop the trial will be made by co-principal investigators ([name], [name], [name]) as informed by the statistical consult.

## Discussion

This paper described the protocol for a randomized wait-list controlled trial to evaluate the effect of the WSTP on MWC skills capacity in children and adolescents, and to explore the influence on MWC use self-efficacy, satisfaction with participation and parents’ perceptions of MWC skills.

Three Canadian sites (Quebec City, Montreal, Halifax) represent major urban centres with access to a large population of children and adolescents who use MWCs. The MWC procurement process in Canada is variable, and there are differences in geography, culture, and climate. In the province of Quebec, MWC are covered by the provincial healthcare system, but services focus mainly on MWC selection and set-up. Observationally, MWCs are replaced about every 5 years, with little follow-up on MWC related services, such as training. However, in Nova Scotia (and other Canadian provinces), wheelchairs are commonly purchased through private insurance, by the family, or obtained through wheelchair recycling programs, with limited access to training, especially for those living in rural areas. This diversity will allow the effectiveness of the WSTP to be evaluated in a variety of clinical contexts and geographical regions, for which site-specific post-hoc exploratory analyses will provide additional insights.

Although an attention-matched control group would provide the most rigorous controlled design, pilot work suggested a high risk of attrition and lack of interest to participate in the study. In fact, parents expressed not wanting to risk their child being allocated to a control group if it meant they would not receive MWC skills training. Given the known benefits of the WSTP in adults [24, 25], strong preliminary evidence in children [26–29], and in effort to mitigate attrition and facilitate recruitment, a wait-list control group was justified for this trial. This design will also reinforce clinical equipoise and reduce the risk of bias associated with lack of equipoise.

Enhancing self-directed mobility through MWC skills training may provide children with the dependent, indoor, community and advanced skills needed to use a MWC, thus could enhance participation in activities that require the use of a MWC (e.g., activities at school, sports, and active play), and reduce risks of acute (e.g., tips and falls) and overuse (e.g., repetitive strain due to poor propulsion techniques) injuries. Moreover, clinicians and community organizations have expressed interest in learning about MWC skills evaluation and training for integrating into clinical practice and community programs. For example, a community based physical activity organizing offering adapted physical activity programs would like to offer wheelchair skills training as a weekly program.

Establishing effect size in a randomized controlled trial will provide evidence to support integration of the WSTP into clinical and community partners to implement the WSTP as part of clinical practice and community-based program offering. Facilitators and barriers to using the WSTP may be explored with therapists and community partners. Implementation of the WSTP into regular clinical practice would ensure training starts early, specifically in fundamental skills (e.g., propulsion and maneuvering) and indoor skills required for getting around in the home and school. Extending MWC skills training into the community may reduce burden on rehabilitation therapists while responding to ongoing training needs as the child develops. For example, children receive new MWC as they grow. Approaches to performing community and advanced MWC skills, such as ascending curbs and steep ramp, may vary depending on MWC configuration and set-up. Moreover, having the opportunity to receive training when receiving a new MWC may enhance skills, safety and self-efficacy. In addition, if the child experiences a tip or fall, availability of wheelchair skills training in the community may provide an opportunity to rebuild skills and confidence on an as-needed basis. Future studies may consider implementation evaluation of the WSTP in clinical practice and ecological evaluations when training provided as a community-based program.

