### Sample size

The sample size was powered to detect a statistically significant difference of 20% between groups [24], using mean change scores from T_1_ to T_2_ in the primary outcome from [name] et al., 2016, which reported a large effect size (Cohen’s d = 1.3) for the WST and a correlation between measures (R^2^) of 0.6 [37]. Based on pilot work, children and adolescents have similar variability in WST capacity scores compared to adults (standard deviation varying from 8 to 20) [26, 27]. However, given the unknown variability associated with age range, a more conservative effect size informed by our pilot work (d = 0.85) and measure correlation (0.60) was chosen. With α = 0.05, and 85% power for between-factors ANCOVA repeated measures design (F-tests) controlling for baseline score (account for function/motor development), a sample size of 18 will be required. Given site variability, each site is powered for primary analysis. G*Power v.3.1.9.2 was used for sample size calculations [38]. Adjusting for a 10% loss to attrition, a total sample size of 60 (20 per site) will be required.

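### Site results are described both as powered for the primary analysis and as post-hoc exploratory; at 18 children per site they lack the stated power, and no treatment-by-site comparison is named to show whether regions differ

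*Protocol article*

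**What the plan says.** Three parts of the protocol article bear on this point.

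- **Sample size.** The inputs are given as follows: "a more conservative effect size informed by our pilot work (d = 0.85) and measure correlation (0.60) was chosen". With α = 0.05 and 85% power, "a sample size of 18 will be required". The section then states: "Given site variability, each site is powered for primary analysis". It concludes: "Adjusting for a 10% loss to attrition, a total sample size of 60 (20 per site) will be required". So 18 is used as the evaluable total at one site, about 9 per arm under 1:1 allocation.
- **Analyses.** The primary comparison is a single ANCOVA of the post-intervention WST capacity score between the two groups. Age, gender and wheelchair experience are to be explored as influences on effect size with linear mixed-effect models. Site is not in that list, and no treatment-by-site term is named.
- **Discussion.** The differences between Quebec and Nova Scotia are presented as a strength that lets effectiveness be evaluated across contexts and regions, for which "site-specific post-hoc exploratory analyses will provide additional insights".

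**The concern.** The same site-level results carry two statuses. In the Sample size section they justify the total of 60, since each site is sized as if it were a trial of its own. In the Discussion they are exploratory. A reader who takes the first statement at face value will expect a conclusive answer from each site.

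Three separate within-site tests also do not answer the question the Discussion raises. Whether training works better in one region than another is a question about the difference between site effects. A significant result at one site beside a non-significant result at another is not evidence of such a difference. If power per site is moderate, that pattern is to be expected even when the true effect is the same everywhere.

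What is at stake is the interpretation of regional results, which the authors hope will support uptake by clinical and community partners. The pooled primary estimate is not affected.

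**Working it through.** **Inputs.** From the Sample size section: d = 0.85, correlation 0.60, α = 0.05 (an F-test on two groups, hence two-sided), stated power 85%, 18 evaluable per site. From the Design section: three sites, 1:1 allocation. One ambiguity: the same paragraph first describes the adult figure as "a correlation between measures (R^2^) of 0.6". If 0.6 is R², then r = √0.6 = 0.775.

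**Step 1: the stated sample size.** The attrition step reproduces: 18/0.9 = 20 per site, and 3 × 20 = 60. The 18 itself does not. With f = d/2 = 0.425 and f² = 0.1806:

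- ANCOVA: λ = f²N/(1 − r²), with N − 3 denominator df. At N = 18 and r = 0.60, λ = 0.1806 × 18/0.64 = 5.08 on (1, 15) df, critical F = 4.54, power 0.56. Reaching 85% needs N = 34 (power 0.85).
- Repeated measures, between factors: λ = f²Nm/(1 + (m − 1)r). At N = 18, m = 2 gives λ = 4.06 and power 0.47; m = 3 gives λ = 4.43 and power 0.51. Reaching 85% needs N = 42 and N = 40.
- ANCOVA with R² = 0.6: λ = 0.1806 × 18/0.40 = 8.13, power 0.76.

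So 18 would serve as a per-arm number (N = 36 gives ANCOVA power 0.87), but not as a site total. Of the variants tried with f = d/2, a total of 18 appeared with inputs the article does not state as chosen. One is the adult d = 1.3 with three measurements and r = 0.6 (power 0.856). Another is a one-sided ANCOVA with R² = 0.6 (power 0.859).

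**Step 2: separate site tests under one common effect.** With equal power p at three independent sites:

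P(all significant) = p³; P(none) = (1 − p)³; P(mixed) = 1 − p³ − (1 − p)³.

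| Reading, 18 per site | p | All | None | Mixed |
|---|---|---|---|---|
| ANCOVA, r = 0.60 | 0.56 | 0.17 | 0.09 | 0.74 |
| Repeated measures, m = 2 | 0.47 | 0.11 | 0.15 | 0.75 |
| Repeated measures, m = 3 | 0.51 | 0.13 | 0.12 | 0.75 |
| ANCOVA, R² = 0.6 | 0.76 | 0.44 | 0.01 | 0.55 |
| Stated power taken as true | 0.85 | 0.61 | 0.003 | 0.38 |

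Simulating the ANCOVA at 9 per arm (30,000 trials of three sites) gave power 0.53 and mixed 0.75 at r = 0.60, and 0.73 and 0.59 at r = 0.775. If all 20 per site are analysed at r = 0.60, the formulas give mixed results 0.71–0.75 of the time.

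**Step 3: what a direct comparison offers.** A 2-df group-by-site test signals a false difference 5% of the time by construction. Its power is low. Assume, for illustration, a true effect of 0.85 SD at two sites and zero at the third, with r = 0.60 and 9 per arm. The variance of a site effect is 0.64 × 2/9 = 0.142. The squared deviations from the mean effect (0.567) sum to 0.482, so λ = 0.482/0.142 = 3.39 on (2, 47) df, and power is about 34%.

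**The case against.** The strongest reply is that the article does not describe the faulty procedure. It names no model for the site analyses, sets no p-value rule for a site, and labels the analyses exploratory. Where it does give a method for effect modifiers, that method is model-based. A group-by-site term is compatible with every word of the Discussion, and a fuller plan, not shown, may contain one. The Sample size sentence may be only a rationale for recruiting 60, since the primary analysis is a single comparison.

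Much of this stands. A reader might infer that regional differences will be decided by which sites reach significance, or that the trial will probably report benefit in one city and none in another. The documents support neither: separate site tests are an inference from the Sample size wording, and how results will be reported is not stated.

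The 74% figure also needs its conditions. The formula cannot exceed 0.75, reached at p = 0.50, so 74% is close to the worst case. Two further arguments carry little weight for exploratory analyses: the lack of joint error control over three tests (1 − 0.95³ = 14% if all sites were null), and the slightly wider intervals from separate fits (half-width 0.80 SD against 0.76 SD with pooled variance).

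The reply does not remove the conflict between the two sections, which lies in the published text whatever a fuller plan says. Nor does it rescue the power claim, which the article's own inputs contradict.

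**Conclusion.** The point holds in a conditional form. The article gives site results two incompatible statuses, and the stronger one is not supported: power per site is about 56% by ANCOVA (47–51% by the repeated-measures formula, 76% if 0.6 is R²) against the stated 85%. If sites are tested separately, a common effect gives a mixed picture about 74% of the time, about 55–59% if 0.6 is R², and 38% at the stated power. On each of these readings, separate site tests are a poor guide to regional variation; only the size of the problem changes.

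This assumes d = 0.85 at every site, 9 evaluable children per arm per site, independent sites and two-sided 0.05. It is a matter of interpretation and labelling. It does not invalidate the pooled primary analysis: with 54 evaluable in total, λ = 0.1806 × 54/0.64 = 15.2 on (1, 51) df, and power is about 0.97 under the same inputs.

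**What to change.** 1. In the Sample size section, remove or restate the claim that each site is powered, so that this section and the Discussion both call site results exploratory.
2. Assess regional variation in one pooled ANCOVA with baseline score, group, site and group-by-site. Report the 2-df interaction test, say that its power is low, and give the three site-specific adjusted differences with 95% confidence intervals from that model.
3. State that no site is declared effective or ineffective from its own p-value.

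The change is to wording and one exploratory model; it needs no extra participants or data. The costs are a less favourable site-level claim and an interaction test that could easily miss a real difference, so a non-significant result must not be read as proof that the sites are alike.

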### Dissemination plan

A multifaceted knowledge translation strategy aims to increase awareness and knowledge and to change clinical and community practice related to wheelchair skills training and evaluation for children and youth. Targeted promotional and knowledge translation materials will be developed throughout the study for all stakeholders in English and French (children who use MWCs, families, clinicians, community professionals) including books, posters, workbooks, videos and infographics, that will be disseminated using several platforms (e.g., print, social media of clinical and community partners). We will work with community partners to customize end-of-grant promotional and awareness videos for MWC skills training to be shared through social media to prepare for implementation. The WSP and community partner websites will be used to disseminate key messages to researchers, clinicians, and the community. A minimum of three peer-reviewed publications will include a research protocol, results of the main trial, and integrated knowledge translation from clinical RCT to community practice. Results from the study will also be presented at national, international and local conferences.

## Data Availability

Data and materials will be made available upon request to the corresponding author.

## Abbreviations

MWC: Manual wheelchairs
WHO: World Health Organization
WSP: Wheelchair Skills Program
WSTP: Wheelchair Skills Training Program
RCT: Randomized controlled trial
OT: Occupational therapist
WST: Wheelchair Skills Test
NP: Not possible
TE: Testing error
MCID: Minimally clinical important difference
WST-Q: Wheelchair Skills Test Questionnaire
WheelCon-M-P: Wheelchair Use Confidence Scale for Pediatric MWC users
WhOM-YP: Wheelchair Outcome Measure for Young People
ANCOVA: Analysis of covariance
CIUSSS-CN: *Centre intégré universitaire de santé et de services sociaux de la Capitale-Nationale*
CRME: *Centre de réadaptation Marie Enfant*
